## Abstract

Recurrent implantation failure (RIF) is a common issue in frozen-thawed embryo transfer (FET). Prior to transfer, uterine endometrial receptivity of FET patients can be assessed using multimodal transvaginal ultrasound indicators to predict the success rate of the current FET cycle. Endometrial blood flow is a crucial element in evaluating endometrial receptivity. MV-FLOW^™^ is an advanced two-dimensional superb microvascular imaging technology that can detect and display blood flow in micro-vessels. The data for this study were obtained from an ongoing cross-sectional study comprising 323 RIF patients and 323 first implantation (FI) patients, who underwent transvaginal ultrasound before FET. We collected basic clinical data and multimodal ultrasound data from these patients as predictive features, with clinical pregnancy as the predictive label, for model training. Based on the above, this study aims to establish and validate a clinical prediction model for FET outcomes using support vector classification (SVC) algorithms, based on MV-FLOW^™^ and multidimensional transvaginal ultrasound imaging features. The objective is to determine the predictive role of multimodal transvaginal ultrasound in embryo transfer outcomes and provide evidence for the clinical application of MV-FLOW^™^.

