Nonetheless, certain scholars harbor reservations about this viewpoint [5] given that the study’s subjects all underwent costly preimplantation genetic testing for aneuploidies (PGT-A) and endometrial receptivity analysis (ERA) diagnostics, limiting their applicability across all in vitro fertilization (IVF) patients. In 2023, the European Society of Human Reproduction and Embryology (ESHRE) [6] recommended a 60% threshold for cumulative predicted implantation opportunity in recurrent implantation failure (RIF) to differentiate between euploid and aneuploid embryo transfers. Pre-transfer multimodal vaginal ultrasound indicators are routinely used in clinical practice to assess endometrial receptivity in FET patients, serving as a diagnostic tool to predict FET success rates. Endometrial blood flow, primarily assessed via 2D ultrasound following the Applebaum criteria [7], is crucial for evaluating blood flow velocity and direction through the Doppler effect. Endometrial blood flow is a crucial aspect of endometrial receptivity assessment, primarily through 2D ultrasound mode, following the Applebaum criteria for detecting and classifying endometrial blood flow signals. Its principle involves utilizing the Doppler effect of ultrasound waves to evaluate blood flow velocity and direction. Specifically, when the ultrasound beam encounters moving red blood cells, it generates a frequency change proportional to the blood flow velocity. By analyzing this frequency change, the blood flow velocity can be calculated, thereby assessing the richness of blood flow and vascular resistance. MV-FLOW^™^ is an advanced spatiotemporal coherent superb microvascular imaging technology capable of detecting and displaying blood flow in small vessels. Studies have shown [8–10] that MV-FLOW^™^ can display low-speed blood flow in normal or diseased tissues (such as tumors), with high sensitivity and resolution. Our previous research [11] observed the effects of acupuncture on MV-FLOW^™^ in RIF patients on the day before implantation, suggesting that MV-FLOW^™^ is a sensitive indicator of endometrial blood flow and that acupuncture can exert immediate regulatory effects on this indicator. However, the predictive value and advantages of MV-FLOW^™^ for embryo transfer remain unclear.

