This study, grounded in a current cross-sectional investigation employing support vector classification (SVC) algorithms, aims to explore: (1) the predictive precision of MV-FLOW^™^ endometrial vascular distribution indices and/or endometrial vascular indices for FET outcomes in RIF patients; (2) the potential of these indices to categorize patients as either successful first implantation (FI) or RIF.

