#### Clinical prediction model

*Machine Learning Algorithm*. In this study, the SVC algorithm was selected for machine learning applications. All computations were executed using the Sklearn package within Python 3.10.

*Data Preprocessing*. Altogether four steps of data preprocessing were applied in this study. First, we will remove the outliers and organize the data. As for missing value filling, we will conduct KNN Imputer for continuous variables, and Simple Imputer for categorical variables. The Spearman correlation analysis was first conducted to evaluate the relationship between all predictive feature variables and clinical pregnancy outcomes (Spearman’s correlation coefficient more than 0.2 were significant). Eventually, we removed low-variance (Variance Threshold = 0.8) variables and highly correlated variables (r^2^>0.8).

*Prediction Variable Selection*. Thereafter, a SVC model was constructed using the remaining feature variables. The filtered feature subset was then input into the established model to rank the feature weights. These weights indicate the contribution of each feature to the determination of the SVC hyperplane. In accordance with the LIBSVM manual, SVC_coef was employed as the feature weight to compute the permutation importance of the features, with the feature exhibiting the maximum value of the mean ± standard deviation being deemed the most valuable predictive indicator.

*Model performance evaluation*. The dataset for the predictive model was partitioned into a training set and an internal validation set in a 7:3 ratio, with internal validation of the model conducted using cross-validation techniques. The accuracy of the classification results was assessed through the use of a confusion matrix. For binary classification tasks, sample cases can be categorized into four scenarios based on their actual class and the predicted class by the trained model: true positives (TP), false positives (FP), true negatives (TN), and false negatives (FN). The model’s accuracy was evaluated using the precision ratio (P) and recall rate (R). Ultimately, the F1 score was employed to synthesize both precision and recall. Additionally, the model’s performance was evaluated using the receiver operating characteristic (ROC) curve and the area under the curve (AUC).

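### The feature ranking meant to show MV-FLOW's value is ill-defined and can change with measurement units, and no step isolates what MV-FLOW adds to conventional ultrasound

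*Protocol article*

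**What the plan says.** All places are in the protocol article.

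- **Purpose.** The Introduction gives the gap as "the predictive value and advantages of MV-FLOW^™^ for embryo transfer remain unclear". Its first aim is "the predictive precision of MV-FLOW^™^ endometrial vascular distribution indices and/or endometrial vascular indices for FET outcomes in RIF patients". The Abstract intends to "provide evidence for the clinical application of MV-FLOW^™".
- **Preprocessing** (Data analysis, Clinical prediction model). "Altogether four steps of data preprocessing were applied in this study". The steps are outlier removal, imputation (KNN for continuous variables), a Spearman analysis against clinical pregnancy with 0.2 as the mark, and a final filter that "removed low-variance (Variance Threshold = 0.8) variables and highly correlated variables (r^2^>0.8". Scaling is not among them.
- **Ranking** (same section, Prediction Variable Selection). An SVC is fitted to the remaining features and the weights are ranked. On how the ranking is computed, the text says "SVC_coef was employed as the feature weight to compute the permutation importance of the features". It then settles which feature comes out on top by a second clause: "with the feature exhibiting the maximum value of the mean ± standard deviation being deemed the most valuable predictive indicator".
- **Performance** (same section). Precision, recall, F1, ROC curve and AUC describe the model as a whole.
- **The index.** The ultrasound acquisition section defines the MV-FLOW index as a ratio of pixel counts. The other features include velocities, a pressure gradient, dimensionless ratios, a volume and 3D vascular indices.

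**The concern.** The ranking rule has three defects. It treats a coefficient and a permutation importance as one quantity, although neither is computed from the other, and a coefficient exists only for a linear kernel. It takes the maximum of an expression that is not a single number. It is applied after a list of steps without scaling, although KNN distances, the SVC penalty and the SVC weights all depend on the units of the features.

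Two analysts could follow the text on the same data and name different leading indices, and the choice between ratio and percent could decide whether MV-FLOW enters the model at all. Even a sound ranking would leave a gap: a rank says how much one fitted model leans on a feature, not how much prediction improves when that feature is added to age, embryo factors and conventional ultrasound.

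**Working it through.** **The plan's own figure.** The sample size section gives 323 RIF patients at a 30% pregnancy rate. With a margin of 0.05 on the overall risk (my assumption; the code is in a supplement not shown), n = (1.96/0.05)² × 0.30 × 0.70 = 1536.64 × 0.21 = 322.7, rounded up to 323. It reproduces. Here it only supplies n and the event rate.

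**1. Variance filter.** A variable confined to 0–1 with mean μ has variance at most μ(1 − μ) ≤ 0.25, which is below 0.8. An MV-FLOW index stored as a ratio is therefore removed whatever its predictive value. In percent the variance is 10,000 times larger, and the index survives once its SD exceeds √0.8 = 0.89 percentage points. At an assumed SD of 0.05 the variance is 0.0025 as a ratio and 25 in percent. With assumed SDs of 0.07 for RI and 0.6 for PI, those features (0.0049 and 0.36) are removed too. If all features were standardised first, each would have variance 1 and the filter would remove none.

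**2. Coefficient and units.** Since w·x = (w/c)·(cx), multiplying a feature by c divides its equivalent weight by c; the penalty on w then shifts the fit further. Illustration, without the filter: linear soft-margin SVC, C = 1, n = 323, 60 datasets. Assumed SDs are MV-FLOW 0.08, PSV 12, EV 1.5, PI 0.6, thickness 2.0. Assumed log odds per SD are 1.0, 0.5, 0.5, 0.3 and 0, with intercept −1.1, so MV-FLOW is strongest by construction.

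| MV-FLOW coding | mean weight (absolute) | first by weight | first by permutation importance |
|---|---|---|---|
| 0–1 | 2.10 | 100% | 88% |
| percent | 0.089 | 0% (mean rank 3.0) | 98% |
| standardised | 0.699 | 98% | 98% |

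The weight ratio is 2.10/0.089 ≈ 24 rather than 100 because the penalty holds back the large weight. Coding thus changes the fit itself, so even permutation importance slips in the first row.

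**3. The same question with the plan's filter.** Two runs used ten features with assumed SDs: thickness 1.8, PSV 12, EDV 3, RI 0.07, PI 0.6, MV-FLOW 0.05 (5 in percent), EV 1.5, VI 6, FI 6, VFI 3. Effects were also assumed, with MV-FLOW truly strongest and coded in percent. Share of datasets in which it ranked first by weight:

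| Preparation | run A | run B |
|---|---|---|
| raw, no filter | 0% | 0% |
| raw, variance filter | 9% | 22% |
| raw, variance filter and Spearman screen | not run | 78% |
| standardised | 84% | 92–96% |

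In run B with the variance filter, the median rank was 2 and the index was in the top two in 77% of datasets.

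**4. The mean ± SD rule.** Let two features have mean importances m₁ < m₂ and SDs s₁, s₂. Ranked by the mean, feature 2 wins. Ranked by mean + SD, feature 1 wins whenever s₁ − s₂ > m₂ − m₁, that is, when it is sufficiently less stable. The text does not say which is meant.

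**5. Contribution of MV-FLOW.** The analyses that touch it are group comparisons, a univariable Spearman coefficient, a rank within one model, and the performance of that whole model. None gives a difference in performance with and without the index.

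**6. Precision of such a comparison.** Hanley–McNeil, assumed AUC A = 0.75: A/(2 − A) − A² = 0.0375 and 2A²/(1 + A) − A² = 0.0804.

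- 30% validation set, about 97 patients with 29 pregnancies: SE = √[(0.1875 + 28 × 0.0375 + 67 × 0.0804)/(29 × 68)] ≈ 0.058, so ±0.11.
- All 323 by cross-validation, 97 pregnancies: SE = √[(0.1875 + 96 × 0.0375 + 225 × 0.0804)/(97 × 226)] ≈ 0.032, so ±0.06.
- Paired difference: SE × √(2(1 − ρ)). For an assumed correlation ρ of 0.9 to 0.5, the half-width is about 0.03 to 0.06.

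**The case against.** - **Scaling is a routine detail that an article may leave out.** No sentence says the data are unscaled. This stands as a limit: the absence is inferred. But the text counts its steps and names all four, so the inference is the plain reading.
- **The text also names permutation importance, and mean and SD are what repeated permutation produces.** This stands. On that reading the unit problem is weak (88–98% across codings). The sentence still ties the quantity to the coefficient and leaves the decision rule undefined.
- **A reader might infer that a strong MV-FLOW index would almost never rank first.** The documents do not support that. The plan's variance filter removes some of the small-scale features that take large raw weights, and the Spearman mark, if it acts as a screen, removes more. The article does not say whether features below 0.2 are dropped.
- **A reader might infer that a worthless index stored as a ratio would often rise to the top.** Under the written plan it cannot, because the variance filter deletes it first.
- **A reader might say MV-FLOW is judged by the ranking alone.** It is not: there are univariable analyses and a whole-model AUC.
- **The aims promise no with/without comparison.** True: the first aim speaks of predictive precision, and advantages appear as a gap in knowledge. Nor would the ranking usually crown a redundant index: in 200 simulated datasets with standardised features, one that only echoed a conventional index (r = 0.85, so r² = 0.72, within the collinearity limit) came first in 4.5%. But an advantage needs a comparator, and the plan supplies none.

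**Conclusion.** The concern holds in limited form. As written, the ranking conflates two quantities, its decision rule is undefined, and on the coefficient reading its result depends on units. The variance filter makes coding decisive: as a ratio the index is removed with certainty, a result that needs no assumption beyond reading 0.8 as a raw-scale variance. In percent it normally survives and tends to be under-ranked. How much depends on assumed SDs and effects: first in 9% to 22% of datasets with the variance filter, 78% in the one run that added a Spearman screen, against 84% to 96% standardised. No single figure should be quoted as the size. If true permutation importance is what will be computed, the unit effect is small, while the undefined rule and the variance filter remain. Separately, MV-FLOW's advantage over conventional ultrasound is not assessed by any stated step. This should be corrected before analysis; it does not invalidate the study.

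**What to change.** 1. Replace the raw-variance filter with a scale-free near-constant check, for instance on the share of identical values. Standardising alone would only make the 0.8 threshold inert for continuous features.
2. Standardise continuous features before KNN imputation and the SVC, with all parameters estimated inside the training folds.
3. Rank by one quantity: mean permutation importance, as drop in AUC on held-out folds, with an interval. Delete the mean ± SD rule and the reference to the coefficient as its source.
4. For the first aim, add a paired comparison of cross-validated AUC in the RIF patients: a base model of clinical features plus conventional 2D/3D ultrasound, against the same model plus the MV-FLOW indices, with a bootstrap 95% CI for the difference. Report it as an estimate; at n = 323 it will be imprecise.

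The cost is revised analysis wording and one further model fit. No extra patients or measurements are needed. The sponsor must accept that the added value may prove small or remain uncertain.

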## Discussion

Angiogenesis plays a pivotal role in the growth of the endometrium and embryo implantation [19,20]. During the transition of the endometrium from the proliferative to the secretory phase, there is a gradual increase in endometrial blood flow, and abundant endometrial blood supply is crucial for successful embryo implantation [21]. Dynamic transvaginal ultrasound monitoring of changes in uterine arteries, endometrium, and sub-endometrial angiogenesis can effectively assess endometrial blood supply. A meta-analysis [22] revealed statistically significant differences in endometrial VI, FI, VFI on the day of embryo transfer, and sub-endometrial vascular FI on the day of human chorionic gonadotropin (hCG) injection between pregnant and non-pregnant women following assisted reproductive technology treatment, suggesting a potential relationship between these blood flow parameters and pregnancy occurrence. However, some studies have questioned the relationship between endometrial blood flow indices under ultrasound and endometrial receptivity. For instance, Mayer et al. [23] found no statistically significant differences in endometrial and sub-endometrial VI, VFI, and FI on the day of transfer between pregnant and non-pregnant women in frozen embryo transfer cycles. Similarly, Zhang et al. [24] reported no statistically significant differences in uterine PI, RI, and endometrial and sub-endometrial VI, FI, VFI on the day of hCG injection between pregnant and non-pregnant groups, as well as between miscarriage and ongoing pregnancy groups, suggesting that blood flow-related parameters of the endometrium and sub-endometrium cannot accurately assess endometrial receptivity.

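### The top indicator is named by largest importance alone, with no chance reference, and the text does not settle whether the earlier Spearman 0.2 step supplies one

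*Protocol article*

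**What the plan says.** All of the following is from the protocol article.

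- **Naming rule** (Data analysis, Clinical prediction model, Prediction Variable Selection). The measure is given as "SVC_coef was employed as the feature weight to compute the permutation importance of the features", and the decision follows in the same sentence, the feature with the largest mean ± SD "being deemed the most valuable predictive indicator". No threshold, null distribution or interval goes with it.
- **Earlier steps** (same section, Data Preprocessing). Every feature is correlated with clinical pregnancy, and "Spearman’s correlation coefficient more than 0.2 were significant". The next sentence lists what is taken out: "we removed low-variance (Variance Threshold = 0.8) variables and highly correlated variables".
- **What is ranked** (Prediction Variable Selection). "The filtered feature subset was then input into the established model to rank the feature weights".
- **Performance** (Model performance evaluation). A 7:3 split, cross-validation, confusion matrix, precision, recall, F1 and AUC are planned for the model. None of them is made a condition for naming the top feature.
- **Use of the result.** The Abstract says the study is to "provide evidence for the clinical application of" MV-FLOW. The Discussion plans to identify the most predictive ultrasound indices, and says that all ultrasound-derived flow parameters will be put in as features.
- **Prior evidence** (Discussion). A meta-analysis found differences in flow indices between pregnant and non-pregnant women. Two further studies found none, and from the second the article draws the suggestion that flow parameters "cannot accurately assess endometrial receptivity".

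**The concern.** Any non-empty set of importances has a largest value. A rule that takes the largest and calls it the most valuable predictor therefore cannot, by itself, return the answer that nothing predicts. The SD attached to a permutation importance usually describes variation over repeated shuffles of one feature in one data set. It does not describe how large the best of many useless features would look by chance.

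The null case is a live one, because the Discussion cites mixed evidence on exactly these indices. The named indicator is also a main product of the study. If the label can be given to a noise feature, an index could be put forward for clinical use without having been shown to predict.

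Whether this can happen as the plan is written depends on what the Spearman step does.

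**Working it through.** **1. The plan's own sample size.** With 30% clinical pregnancy and an assumed margin of ±0.05 on the overall risk, n = 1.96² × 0.3 × 0.7 / 0.05² = 322.7, rounded up to 323. This matches the stated 323. Expected pregnancies are 0.3 × 323 ≈ 97. A 7:3 split gives about 226 training and 97 validation women.

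**2. Number of features (assumption).** Counting the ultrasound acquisition section gives 8 arterial indices, VI^MV, 4 three-dimensional indices, thickness, morphology, motion and the colour-flow type: 8 + 1 + 4 + 3 + 1 = 17. With the categorical items dummy-coded (2 terms for morphology, 4 for motion, 2 for flow type) the count is 8 + 1 + 4 + 1 + 2 + 4 + 2 = 22. Clinical features come on top. I use a range of 10 to 40, treated as independent.

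**3. Reading A: the 0.2 mark does not remove features.** A non-empty set is ranked and its maximum named. In simulated studies with no association (323 women, 30% pregnant, 226/97 split, linear SVC, C = 1, 10 shuffles per feature):
- The largest absolute coefficient was unique in 100% of studies for 10, 17 and 25 features.
- With AUC-scored importance on the validation women, the feature with the largest mean + SD was never tied, and its mean importance was positive in 93 to 99% of studies.
- With 22 features and balanced class weights, the winning mean AUC loss averaged 0.031 on the validation women, with a shuffle SD of 0.020, although the true AUC is 0.50. Its 95th percentile by chance was 0.057.
- With accuracy scoring and no class weights, several or all features tied at the maximum, in most cases at zero, in 100%, 94% and 74% of studies for 10, 17 and 25 features. Permutation importance then gives no unique winner, although the coefficients still do.

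**4. Reading B: features with |rho| ≤ 0.2 are dropped.** Under no association, t = r√[(n − 2)/(1 − r²)].
- n = 323: t = 0.2 × √(321/0.96) = 3.66, two-sided P = 0.0003 per feature.
- n = 226: t = 0.2 × √(224/0.96) = 3.06, two-sided P = 0.0025 per feature.

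The chance that at least one of k features survives is 1 − (1 − P)^k:

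| k | Screen on all 323 | Screen on 226 training women |
|---|---|---|
| 10 | 0.3% | 2.5% |
| 17 | 0.5% | 4.2% |
| 25 | 0.7% | 6.1% |
| 40 | 1.2% | 9.6% |

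If only positive coefficients above 0.2 count, as the literal wording has it, these figures roughly halve. On reading B, about 90 to 99.7% of null studies have nothing to rank and name no winner.

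**5. Which reading does the text support?** The verb for removal is used only for low variance and collinearity, and those two steps are enough to explain a filtered subset. The Discussion's intention to enter all flow parameters also points to reading A. Against that, a 0.2 mark described as significant and followed by a filtered subset can be read as a screen. The text favours A but does not settle it.

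**6. The second aim.** The Introduction and Study design also set out to separate successful first-implantation patients from RIF patients. The Spearman step is described against clinical pregnancy, so on either reading it gives no chance reference for that label.

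**The case against.** The strongest reply is that the Spearman step already is a chance reference, and a strict one: 3.66 null standard errors at n = 323. A reader might infer from the bare maximum that a winner is named in every null study. The documents do not support that without a condition. It holds on reading A and fails on reading B. This part of the objection stands.

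A second reply is that being most valuable is a relative label, not a significance claim, and that the planned AUC, F1 and cross-validation show separately whether the model works. A validated AUC near 0.5 would indeed warn an attentive reader, and the Discussion makes the clinical implications conditional on the predictions proving accurate. But the plan calls the feature a predictive indicator, and no performance result can withhold that name.

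Third, the simulated importances rest on AUC scoring, class weights, C and independent ultrasound-only features, none of which the article states. Clinical features also compete in the ranking, so when no ultrasound index predicts, the winner may be a genuine clinical predictor. Both points stand, and the importances are illustrative only.

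Finally, a condensed article may leave importance intervals to a fuller plan. That would answer a complaint about missing detail. Here the decision rule itself is printed, and it is complete as a bare maximum.

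**Conclusion.** The concern holds in conditional form. The naming rule has no chance reference of its own and is not tied to validated performance. Unless the 0.2 mark removes features, a top feature is named even when nothing predicts. If it does remove them, the chance that a null study has anything to rank is about 0.3 to 1.2% (screen on 323 women) or about 2.5 to 10% (screen on 226), for 10 to 40 independent features. The second aim is unprotected on either reading.

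It would go too far to say that the study is bound to name a noise feature, or that a winning AUC loss near 0.03 is what it would report. The first depends on an unsettled reading, and the second on assumed settings. Sample size and recruitment are not affected. The point should be corrected before analysis because the conclusion about MV-FLOW draws on the ranking.

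**What to change.** 1. State whether the Spearman 0.2 mark removes features and whether its absolute value is meant. If it removes features, apply it within the training data only.
2. Call the top feature predictive only if both conditions hold: the validated AUC of the whole pipeline has a lower 95% limit above 0.5; and the feature's importance exceeds the 95th percentile of the maximum importance when the full pipeline is re-run on shuffled outcome labels, for example 1,000 times. The second condition alone holds false naming to about 5% of studies in which nothing predicts. State the scoring metric and the data on which importance is computed.
3. Otherwise report the feature only as top-ranked, and state that no indicator was shown to predict.
4. Apply the same rule to the second aim, shuffling its own label.

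The cost is computing time and a few sentences of analysis text. The downside is that the study may have to report that no indicator qualifies.

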#### Sample size calculation

This study is a cross-sectional trial to establish a predictive model for endometrial receptivity and pregnancy outcomes using SVC to predict clinical pregnancy. The ultrasound assessments of uterine arteries and endometrial thickness are crucial for pre-implantation evaluation of endometrial receptivity, a study involving 78 FET patients (resulting in 45 clinical pregnancies, 57.7%) utilized elastic ultrasound imaging and nine predictive indicators based on basic information, achieving a predictive accuracy of 76.92% [15]. Sample size estimation was conducted using “pmsampsize” in R software [16]. According to the definition of RIF, at least two failed ETs were diagnosed as RIF. Assuming a clinical pregnancy rate of 30%, a minimum of 323 RIF patients were required for sample estimation. In a 1:1 ratio, 323 FI patients were also included. The code for sample size calculation is referenced in S1 Fig.

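### The plan needs at least 323 RIF patients to develop the model and enrols exactly 323, but a 7:3 split leaves about 226 of them for training

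*Protocol article*

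**What the plan says.** Under Sample size calculation, the protocol article gives the purpose of the study as to "establish a predictive model for endometrial receptivity and pregnancy outcomes using SVC to predict clinical pregnancy". The method is named: "Sample size estimation was conducted using “pmsampsize” in R software". The result follows: "Assuming a clinical pregnancy rate of 30%, a minimum of 323 RIF patients were required for sample estimation". The FI group has no calculation of its own: "In a 1:1 ratio, 323 FI patients were also included". No allowance is stated for a held-out set or for records lost in cleaning, so the stated minimum and the planned RIF enrolment are the same number.

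Under Clinical prediction model, in the paragraph on model performance evaluation, the model data set is "partitioned into a training set and an internal validation set in a 7:3 ratio", and the sentence continues "with internal validation of the model conducted using cross-validation techniques". The text does not say whether cross-validation runs inside the 70% or over all patients, or whether a final model is refitted on everyone. The preprocessing paragraph adds that outliers are removed first, without a number.

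**The concern.** A minimum size for establishing a model applies to the patients on whom the model is fitted. If the whole enrolment equals that minimum and 30% is then set aside, the model is fitted on fewer patients than the plan says it needs. The set-aside part is also small for measuring performance, because it holds only about 29 pregnancies.

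Prediction of FET outcome in RIF patients is the first aim in the Introduction, so the shortfall falls on the main result. The same 323 patients could serve both development and internal validation more efficiently.

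**Working it through.** **Inputs.** From Sample size calculation: pregnancy rate p = 0.30 and 323 RIF patients. From Clinical prediction model: a 7:3 split. Assumed, because the code is in a supplementary figure that is not shown: a margin of 0.05 for the overall risk, taken as the software default. Also assumed, for illustration: AUC values from 0.70 to 0.80 and a recall of 0.75.

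**Step 1: reproduce 323.** Precision of the overall outcome risk: n = (1.96/margin)² × p(1 − p).
- Margin 0.05: (1.96/0.05)² × 0.30 × 0.70 = 1536.64 × 0.21 = 322.7, rounded up to 323. This matches the stated figure.
- Other margins do not match: 0.045 gives 0.8067/0.002025 = 398.4 (399), and 0.055 gives 0.8067/0.003025 = 266.7 (267). Here 0.8067 = 1.96² × 0.21.

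The match suggests that this criterion set the number. Any criterion that depends on the number of predictors and on expected discrimination cannot be checked, because the article does not give those inputs.

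**Step 2: apply the split to the RIF patients.**
- Training: 0.7 × 323 = 226.1, about 226; pregnancies 0.30 × 226 = 67.8, about 68.
- Validation: 0.3 × 323 = 96.9, about 97; pregnancies 0.30 × 97 = 29.1, about 29.
- Shortfall in training: 1 − 226/323 = 0.30.
- To have 323 in training under a 7:3 split: 323/0.7 = 461.4, so 462 RIF patients.

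**Step 3: the criterion at the reduced sizes.** Half-width = 1.96 × √(0.21/n).
- n = 323: 0.050
- n = 226: 0.060
- n = 97: 0.091

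**Step 4: precision of performance measures, if they are read from the 97.** Hanley-McNeil: SE² = [A(1 − A) + (n₁ − 1)(Q₁ − A²) + (n₀ − 1)(Q₂ − A²)]/(n₁n₀), with Q₁ = A/(2 − A) and Q₂ = 2A²/(1 + A). Here n₁ is the number of pregnancies and n₀ the number of non-pregnancies.

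Worked case, A = 0.70, 29 and 68: Q₁ = 0.5385, Q₂ = 0.5765. SE² = (0.21 + 28 × 0.0485 + 67 × 0.0865)/1972 = 0.00373, SE = 0.061, half-width 1.96 × 0.061 = 0.120.

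| Assumed AUC | Half-width, 97 patients (29/68) | Half-width, all 323 (97/226) |
|---|---|---|
| 0.70 | 0.120 | 0.065 |
| 0.75 | 0.114 | 0.062 |
| 0.80 | 0.105 | 0.057 |

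The right-hand column is approximate. The formula treats the 323 as independent patients scored by one fixed model, whereas cross-validated predictions come from models fitted on overlapping data.

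For recall, which the article names as a performance measure, an assumed 0.75 on 29 pregnancies has a half-width of 1.96 × √(0.75 × 0.25/29) = 0.16.

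**The case against.** **Cross-validation is named in the same sentence.** If it ran over all 323 and the final model were refitted on all 323, the shortfall would vanish. That stands as a possibility. But the text describes a partition into training and validation sets and states no refit. If cross-validation stays inside the 70%, the shortfall is real; if it covers everyone, the split serves no stated purpose. An article may leave such detail to the full protocol or SAP, but here it fixes both the minimum and the split itself, and the two do not fit.

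**The data set may be the pooled 646.** The Abstract can be read that way, with training on 0.7 × 646 = 452, above 323. The Introduction's first aim and Study design tie outcome prediction to RIF patients, and the minimum is stated in RIF patients, so the RIF-only reading is better supported. It is still a reading.

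**The loss is modest on the criterion that gives 323.** This is fair: the margin moves from 0.050 to 0.060, and it concerns the average pregnancy rate, not discrimination. A 7:3 split is also common practice and not invalid in itself.

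**Two stronger readings are tempting.** A reader might infer that the headline AUC will come from 29 pregnancies in one random split. The article does not say so: it names cross-validation, does not say which patients the AUC is computed on, and introduces AUC after precision, recall and F1. A reader might also turn the shortfall into a number of predictors that the training set can no longer support. That needs a c-statistic or R², and the article gives neither. The earlier study it cites is described by "nine predictive indicators based on basic information, achieving a predictive accuracy of 76.92" percent, which is an accuracy and cannot stand in for a c-statistic.

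**Conclusion.** The point holds as an inconsistency between the sample size section and the model evaluation section. On the RIF-only reading, and without a stated refit, the model is developed on about 226 patients, 30% fewer than the plan's own minimum. Any removal of outlying records lowers this further by an unknown amount.

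The 0.060 margin rests on the assumed 0.05 default, which reproduces 323 exactly. The loss of precision in performance is conditional: it applies if performance is read from the 97 held-out patients. In that case the AUC interval is a little under twice as wide as the approximate one for all 323. The documents do not settle whether performance will be read that way, and that is part of what needs correcting.

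**What to change.** Drop the 7:3 hold-out. Fit the final model on all 323 RIF patients, and estimate performance by repeated nested cross-validation or by bootstrap optimism correction. Every preprocessing, selection and tuning step should be repeated inside each resample. Report the resulting AUC with a 95% confidence interval. State plainly that the outcome model is built in RIF patients, so that the Abstract agrees with the other sections.

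If the split is kept, say in Sample size calculation that the development sample is about 226, below the stated minimum of 323, and say how cross-validation relates to the split and whether the model is refitted on all patients.

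The first option costs some rewording and more computing time and needs no extra patients. The second costs wording only but leaves the shortfall in place.
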